### Interventions

#### Intervention Program

Participants will complete 12 training sessions (twice weekly) spread over 7 weeks. The first week will be devoted to familiarization with the exercise protocol, while the subsequent 6 weeks will correspond to the actual intervention phase. Assessments will be conducted at baseline, immediately after the intervention is completed, and at a 4-week follow-up. The 4-week follow-up is included to evaluate the short-term maintenance of physical and psychological effects after the intervention; however, this timeframe does not allow conclusions regarding the long-term sustainability of behavior and psychological changes.

The groups will receive the designated intervention according to the following allocations: HBG, FxF, or CG. The 2 interventions will be compared to estimate the magnitude of differences in symptom relief and other outcomes, rather than to formally test equivalence. Participants allocated to the CG will be instructed to maintain their usual lifestyle and PA habits throughout the 7-week intervention period and the 4-week follow-up, and not to start any new structured exercise program (eg, supervised gym training, personal training, online exercise programs, or new exercise routines performed ≥2 times/wk). CG participants will receive no supervised training sessions or exercise prescription during the study period. To monitor potential contamination, all participants (including CG) will be asked at baseline, postintervention, and follow-up whether they started, stopped, or substantially changed their PA routines during the study. In addition, CG participants will be contacted weekly by message or phone call to confirm that no new structured exercise program was initiated and to record any relevant changes in PA behavior. Any initiation of a new structured exercise program during the trial will be documented and reported. These participants will remain in the intention-to-treat (ITT) analysis, and a per-protocol sensitivity analysis excluding participants with major protocol deviations will be conducted.

In addition to exercising, participants will receive educational instruction about their disease, surgery, eating habits, and PAs. A summary of the frequency, intensity, type, time, volume, and progression (FITT-VP) principles, as well as the progression factors proposed for each program modality can be found in Table 2. Researchers who participate in the clinical trial will undergo specific training to standardize the intervention. The professionals have more than 10 years of experience in the field of physical exercise and prehabilitation for individuals with obesity.

**Table 2. T2:** Principles for each exercise modality group.

Principles	Home-based group	Face-to-face group	Control group
Frequency	2 d/wk	2 d/wk	Maintain usual physical activity habits (no new structured exercise program)
Intensity	Moderate	Moderate	Maintain usual physical activity habits (no new structured exercise program)
Time or volume	Aerobic: 30 min of aerobic training on a treadmill, stationary bike, or walking outdoors Resistance training: 7 exercises targeting the major muscle groups 3 sets of 8-10 repetitions for each exercise Approximately 2 s for each concentric contraction and 4 s for eccentric phases 40‐60 s between sets ~40 min per section	Aerobic: 30 min of aerobic training on a treadmill Resistance training: 7 exercises targeting the major muscle groups 3 sets of 8-10 repetitions for each exercise Approximately 2 s for each concentric contraction and 4 s for eccentric phases 40‐60 s between sets ~40 min per section	Maintain usual physical activity habits (no new structured exercise program)
Progression factors^a^	Aerobic: Speed Slope of the surface Resistance training: Load (body weight vs external load) Coordination element The number of exercises, sets, and repetitions	Aerobic: Speed Slope of the surface Resistance training: Load (external load; machines) Coordination element The number of exercises, sets, and repetitions	Maintain usual physical activity habits (no new structured exercise program)

a Progression: Aerobic training will involve 5%-10% increases in speed or incline every 2 wk (target: 60%-70% Heart Rate Reserve (HRR); Borg CR-10 scale=4-6). Resistance training will involve ~5% load increases after achieving 10 repetitions, maintaining 3×8-10 repetitions with 40-60 s of rest.

Intervention fidelity will be ensured through standardized training of the professionals involved, structured intervention protocols, and systematic documentation of session delivery. For the HBG, asynchronous video verification will also be used to assess exercise execution and adherence. Participants will be asked to submit video recordings of selected sessions, which will be reviewed by the research team to ensure correct performance and fidelity to the prescribed protocol.

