### Eligibility Criteria

Individuals of both genders with grade III (severe) obesity who meet the following criteria will be included in the research: (1) BMI>40 kg/m^2^, (2) indication for BMS, (3) formal indication for preoperative physical therapy signed by the BMS surgeon, in accordance with the multidisciplinary guidelines for BMS, (4) absence of comorbidities that compromise safety or the ability to perform the exercises and functional tests, and (5) no participation in any structured exercise program in the past 3 months. To ensure equitable access and diversity, recruitment will be stratified to achieve a sample composition of 50% low-income individuals (defined as monthly household income per capita ≤0.5 minimum wage or total household income ≤3 minimum wages) and 20% residents of rural areas. In addition, participants will be excluded if they meet any of the following criteria: (1) presence of a pacemaker, history of myocardial infarction within the previous 3 months, or unstable angina pectoris; (2) sustained or episodic cardiac arrhythmias aggravated by PA, symptomatic peripheral vascular disease, or any clinical condition representing a risk (eg, inability to safely tolerate heart rate increases >20 beats/min during exercise); (3) clinical diagnosis of acute or chronic respiratory diseases that compromise the safety of physical tests (eg, COPD and asthma with remodeling) or peripheral oxygen saturation (SpO₂) <92% during the 6-minute walk test (6MWT); (4) history of previous BMS or abdominal or thoracic surgery within the previous year; (5) abusive use of or chemical dependence on psychoactive substances (including alcohol and illicit drugs), according to clinical criteria or previous diagnosis; (6) cognitive or physical changes that prevent performance of the tests; and (7) initiation of another form of physical training during the intervention period.

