#### Home-Based Program

The protocol will consist of 2 parts: aerobic training and resistance training, and it will last approximately 70 minutes and be performed twice a week on alternate days. The training program was developed specifically for individuals with obesity and can be applied in any environment.

At the beginning of the program, one of the researchers will meet with the participants online (via Google Meet) to explain how the training protocol will be conducted and how the exercises should be performed, and to answer any questions that may arise. Additionally, the meeting will be recorded and made available for participants to access, along with specific videos explaining each exercise. Participants will also have direct contact with the training supervisor for assistance with exercise execution. To monitor the training sessions, participants will be instructed to send a message informing the research team of the completion of the exercises and the time, and the researchers will collect this information weekly. The exercise program will consist of 30 minutes of aerobic training on a treadmill, stationary bike, or walking outdoors, followed by 30 minutes of strength exercises. The Borg scale (CR-10) will be used to monitor exercise intensity, and it is recommended that effort be maintained between 4 and 6, considered a moderate zone of effort, for both aerobic and strength exercises [39], or a 5% increase in speed or incline will be implemented every 2 weeks and in the load of resistance exercises after mastering 10 repetitions (3 sets of 8-10 repetitions, 40-60 seconds of rest). The strength exercises for the upper limbs will include arm flexion (inclined), cable row, and shoulder press, and those for the lower limbs will include free squats, lateral lunges, stepping hip thrusts, and plantar flexions. The exercises can be adapted if the participant has any mobility restrictions or is unable to perform any of the exercises.

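### Controls are asked weekly about new exercise programs and the exercise arms only at visits, so recorded initiation, and any per-protocol exclusion based on it, is expected to be more complete in controls

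*Protocol article*

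**What the plan says.** All citations are to the protocol article.

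- **Common enquiry (Intervention Program).** "all participants (including CG) will be asked at baseline, postintervention, and follow-up whether they started, stopped, or substantially changed their PA routines".
- **Extra enquiry, controls only (same section).** "CG participants will be contacted weekly by message or phone call to confirm that no new structured exercise program was initiated". The article does not say when these contacts end. The instruction to controls runs "throughout the 7-week intervention period and the 4-week follow-up, and not to start any new structured exercise program".
- **The event (same section).** "Any initiation of a new structured exercise program during the trial will be documented and reported". This wording is not limited to one arm. Eligibility Criteria, exclusion item 7, names "initiation of another form of physical training during the intervention period" for participants generally.
- **Use in the analysis (Intervention Program).** Participants who start a program stay in the intention-to-treat analysis, and "a per-protocol sensitivity analysis excluding participants with major protocol deviations will be conducted".
- **Regular contact in the exercise arms.** Home-based participants are to "send a message informing the research team of the completion of the exercises and the time, and the researchers will collect this information weekly" (Home-Based Program). They also submit videos of selected sessions and use app records. For the face-to-face arm, attendance and training loads are recorded. All of this is described for the prescribed sessions. None of it is described as a question about outside programs.

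**The concern.** One event, defined for every arm, is looked for at different intensity by arm. The baseline question cannot pick up a program started after randomization. An exercise-arm participant therefore has two occasions to report one, with recall over up to 7 weeks and then 4. A control has the same two occasions plus a weekly prompt.

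Two outputs are exposed. The first is the reported frequency of new programs by arm, if all sources are pooled. The second is the per-protocol sensitivity analysis, if a new program counts as a major deviation. Self-starters would then be taken out more thoroughly from controls than from the exercise arms. Because a lower HADS score is better, leaving more self-starters in the exercise arms flatters the programs. The problem arises at data collection, so events that were never asked about cannot be recovered at analysis.

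**Working it through.** The plan gives no figure to reproduce, so the check has two parts: the schedule of enquiry, and an illustration of what it could do.

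**Schedule after baseline**

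| | Visit questions | Weekly question on new programs |
|---|---|---|
| Control | 2 | 7 if it stops with the intervention, 11 if it runs through follow-up (7 + 4) |
| Home-based | 2 | none described |
| Face-to-face | 2 | none described |

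**Inputs.** From the article: 60 participants allocated 1:1:1, so 60/3 = 20 per arm. Assumed, not in the article: a true initiation proportion s = 0.20 in every arm (4 of 20); overall detection d of 0.90-0.95 in controls and 0.50-0.70 in the exercise arms; starters scoring 0.5-1.0 SD lower on HADS, equally in all arms.

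**Recorded rate = s × d.**
- Controls: 0.20 × 0.90 = 18% to 0.20 × 0.95 = 19% (3.6 to 3.8 of 20).
- Exercise arms: 0.20 × 0.50 = 10% to 0.20 × 0.70 = 14% (2.0 to 2.8 of 20).

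The gap is 0.8 to 1.8 participants per arm for identical behaviour.

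**Starters left in the per-protocol set = s(1 − d)/(1 − sd)**, if every detected starter is excluded.
- d = 0.95: 0.010/0.81 = 0.012
- d = 0.90: 0.020/0.82 = 0.024
- d = 0.70: 0.060/0.86 = 0.070
- d = 0.50: 0.100/0.90 = 0.111

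**Shift = difference in retained fraction × HADS difference.**
- Smallest: (0.070 − 0.024) × 0.5 = 0.023 SD
- Largest: (0.111 − 0.012) × 1.0 = 0.099 SD
- Middle (d = 0.925 against 0.60): 0.015/0.815 = 0.018 and 0.080/0.88 = 0.091; the difference of 0.073 gives 0.036 to 0.073 SD

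**Sensitivity to the detection model.** Let v be the chance that the visit questions elicit a program and w the chance that one weekly contact does, for a program spanning two weekly contacts. The ratio of recorded rates, control to exercise arm, is [1 − (1 − v)(1 − w)²]/v. For w = 0.3 to 0.5:
- v = 0.5: 1.51 to 1.75
- v = 0.7: 1.22 to 1.32
- v = 0.9: 1.06 to 1.08
- v = 1.0: 1.00

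With the same schedule in every arm, and each question working equally well in each, the ratio is 1.00 whatever v and w are.

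**The case against.** The strongest case against has five parts.

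1. **A common question already exists.** A reader might infer that contamination rates cannot be compared between arms at all. The documents do not support that, because rates from the visit question put to everyone are comparable. What stands is that the article does not confine the between-arm report or the exclusions to that source.
2. **The home-based versus face-to-face contrast.** A reader might infer that this comparison is biased too. Both arms receive the same visit questions, so there is no differential enquiry between them. Extra training may be missed in both, but that has no demonstrated direction.
3. **The same act is not the same deviation in each arm.** Only controls are told not to start a program through the 4-week follow-up; exclusion item 7 covers the intervention period only. The education videos encourage lasting activity, so new exercise in the exercise arms after week 7 is partly intended. Closer watch on the untreated arm is defensible. This stands for weeks 8-11 but does not explain the difference during the intervention period.
4. **The per-protocol link is inferred.** The article does not define a major deviation, which is commonly left to a fuller document. That a new program leads to exclusion is read from the order of the sentences. This stands, so the consequence is conditional.
5. **The effect is small.** The standard error of a simple two-arm difference is √(2/20) = 0.32 SD with 20 per arm, or √(2/14) = 0.38 SD with 14 per arm (42/3 after dropout). A shift of 0.023 to 0.099 SD is about 6% (0.023/0.38) to 31% (0.099/0.32) of one standard error. It would shrink if extra training adds less in people already training twice weekly. This stands.

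**Conclusion.** The asymmetry is stated outright in the Intervention Program section, and no other described contact offsets it. Its consequence is an expected difference, not a certain one: recorded initiation is higher in controls for equal behaviour unless recall at the two later visits is complete. If initiation leads to per-protocol exclusion, that sensitivity analysis tilts toward the programs by about 0.02 to 0.10 SD. This rests on the assumed 20% initiation, 90-95% against 50-70% detection, and a 0.5-1.0 SD HADS difference. None of these comes from the documents.

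A reader might also infer that the main result is at risk. It is not, because the intention-to-treat analysis keeps these participants whether or not their program is detected. The point is a modest one, worth acting on because the remedy is cheap and must be in place while data are being collected.

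**What to change.** During the 7-week intervention period, ask the same weekly question about new structured exercise, with the same wording, in all three arms. Use the home-based arm's weekly message, one face-to-face session per week, and the existing control contact.

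State that between-arm rates of new programs, and any per-protocol exclusion for new training, rest only on enquiries common to all arms. That means the weekly question plus the visit question for the intervention period, and the visit question alone for weeks 8-11, for which no weekly contact with the exercise arms is described. If weekly control contacts continue through follow-up, report what they alone find separately.

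Cost: one added question per week in the exercise arms, carried by contacts that already take place. The downside is that programs found only by weekly control contacts during follow-up are not used for exclusion.

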#### Home-Based Program

The protocol will consist of 2 parts: aerobic training and resistance training, and it will last approximately 70 minutes and be performed twice a week on alternate days. The training program was developed specifically for individuals with obesity and can be applied in any environment.

At the beginning of the program, one of the researchers will meet with the participants online (via Google Meet) to explain how the training protocol will be conducted and how the exercises should be performed, and to answer any questions that may arise. Additionally, the meeting will be recorded and made available for participants to access, along with specific videos explaining each exercise. Participants will also have direct contact with the training supervisor for assistance with exercise execution. To monitor the training sessions, participants will be instructed to send a message informing the research team of the completion of the exercises and the time, and the researchers will collect this information weekly. The exercise program will consist of 30 minutes of aerobic training on a treadmill, stationary bike, or walking outdoors, followed by 30 minutes of strength exercises. The Borg scale (CR-10) will be used to monitor exercise intensity, and it is recommended that effort be maintained between 4 and 6, considered a moderate zone of effort, for both aerobic and strength exercises [39], or a 5% increase in speed or incline will be implemented every 2 weeks and in the load of resistance exercises after mastering 10 repetitions (3 sets of 8-10 repetitions, 40-60 seconds of rest). The strength exercises for the upper limbs will include arm flexion (inclined), cable row, and shoulder press, and those for the lower limbs will include free squats, lateral lunges, stepping hip thrusts, and plantar flexions. The exercises can be adapted if the participant has any mobility restrictions or is unable to perform any of the exercises.

#### Face-to-Face Program

Two researchers with experience in interventions for individuals with obesity will conduct the training sessions at the physiotherapy clinic at UDESC. The sessions will be held in the afternoon and last approximately 70 minutes. The first week will be dedicated to familiarizing participants with the exercise protocol.

Initially, participants will perform 30 minutes of aerobic exercise (treadmill or stationary bike). Once this stage is complete, they will begin a protocol of strength exercises, which will include arm flexion (incline), cable row, and shoulder press. The exercises for the lower limbs will be free squats, lateral lunges, stepping hip thrusts, and plantar flexions, and participants will perform the training in the same manner as the HBG. The loads from all training sessions of the FxF group patients will be recorded, with patients being encouraged to reach concentric failure (ie, the inability to perform one more repetition) in the last series, as prescribed. We chose to prescribe training using maximum repetitions, where the number of repetitions to be performed is fixed and load variations occur based on this reference. A progressive increase in the load level will be initiated when the patient correctly performs the exercises with an ideal movement pattern for 2 consecutive days. Figure 2 presents an illustration of the resistance exercises.

**Figure 2. F2:**
[figure not shown]
Illustration of resistance exercises.

#### Health Education

The health education intervention will consist of 3 previously recorded videos, which will be made available after the week of familiarization, between the second and third weeks of the intervention, and between the fourth and fifth weeks of training.

The sessions will be recorded by physiotherapists and will address essential aspects of the relationship between PA and BMS. The videos will each be a maximum of 10 minutes long and will be structured to achieve the following objectives: (1) understand the importance of PA in the context of BMS, (2) identify and overcome barriers to the regular practice of PA, (3) learn behavioral and cognitive strategies to establish a more active lifestyle, and (4) create a personalized action plan, with realistic and sustainable goals.

Each video will address the 3 pillars of the self-determination theory (SDT): autonomy, competence, and relatedness, in addition to the steps called the “5As”: assess, advise, agree, arrange, and assist [40-42]. To ensure intervention fidelity and quality, participant engagement will be monitored via video analytics (defining adherence as ≥80% viewing completion). Furthermore, the content has been culturally adapted to the Brazilian context, featuring Portuguese audio with subtitles for accessibility. To specifically address and mitigate obesity-related stigma, self-compassion strategies have been embedded throughout the video content, reinforcing the “autonomy” pillar.

Table 3 provides a detailed view of the contents of each session, aligning with the pillars of the SDT and the steps of the “5As.”

**Table 3. T3:** Content of health education videos.^a^

Content	Integration with SDT^b^	5As^c^
Health education 1: Get moving: the first step to change^d^		
Introduce the program and integrate participants Explain the importance of PA^e^ in prehabilitation for BMS^f^ Discuss the impacts of a sedentary lifestyle and the benefits of an active lifestyle Reflect on individual perceptions, barriers, and motivations related to PA Establish progressive short-, medium-, and long-term goals Create an individualized plan to support ongoing engagement.	Autonomy: personal choices about where to begin Competence: highlighting benefits and small past victories Relationships: welcoming and integrating into the group	Assess: identify history, routine, barriers, and facilitators Advise: offer guidance on the benefits of PA and risk mitigation
Health education 2: Building habits and overcoming barriers		
Teach participants how to establish an active routine and differentiate it from structured PA Identify positive environmental cues that can increase PA Explore strategies to eliminate indicators of inactivity and encourage active habits Introduce the concept of positive reinforcement to make PA more enjoyable Identify solutions to common obstacles (eg, lack of time, fatigue, low motivation)	Autonomy: the participant chooses their goals and strategies Competence: training skills to maintain an active routine Relationships: support from the team and peers	Agree: co-define realistic goals aligned with the participant’s values Assist: teach self-monitoring, action planning, and coping skills, positive reinforcement, and practical environmental adjustments
Health education 3: Committing to change		
Differentiate between extrinsic and intrinsic rewards for maintaining PA Recognize sources of support and strategies for maintaining long-term motivation Formalize a personal contract to commit to behavior change	Autonomy: commitment contract and adjustments made by the participant Competence: recognizing achievements and consolidating self-efficacy Relationship: mobilizing ongoing social support	Arrange: organize follow-up, review and adjust goals, consolidate support networks, and schedule follow-ups

a The health education intervention will be developed by the authors themselves and offered to both intervention groups, aiming to provide participants with knowledge and practical tools to increase their adherence to the exercise program, thereby promoting a more active lifestyle before undergoing BMS.

b SDT: self-determination theory.

c 5As: assess, advise, agree, arrange, and assist.

d Before the start of the exercise intervention.

e PA: physical activity.

f BMS: bariatric and metabolic surgery.

